### Recruitment {15}

All patients scheduled for surgery in one of the study sites will be screened whether eligible for inclusion. The screening will be performed by the patient’s main physician, and after eligibility is confirmed, a member of the study team will approach the patient. The enrollment period will extent over 24 months or longer if needed. The enrollment rate will be dependent on the study site. We expect a combined (multi-center) recruitment rate of 5 patients per month. To monitor and improve recruitment, patients eligible, but not recruited for the study, will be identified and analyzed to determine the reason for not participating in this study.

## Assignment of interventions: allocation

### Sequence generation {16a}

Participants will be randomized into two groups (1:1 allocation ratio) using the randomization tool in Castor EDC (Castor EDC, Ciwit BV, Amsterdam, The Netherlands). Variable block randomization will be used, stratified by study site. The block size will be set to 2, 4, and 6 as the possible minimum number of inclusions per center is 16. The study team is always concealed of the sequence of randomization, current randomization or previous randomizations.

### Concealment mechanism {16b}

This is not applicable, as the randomization is done digitally in the Castor EDC (Castor EDC, Ciwit BV, Amsterdam, The Netherlands) environment without the ability to see the randomization process by the study team.

### Implementation {16c}

The allocation sequence is generated on demand during the randomization process in Castor EDC (Castor EDC, Ciwit BV, Amsterdam, The Netherlands) and are automatically assigned to the randomized participants.

## Assignment of interventions: blinding

### Who will be blinded {17a}

The randomization result will be held in the Castor EDC program which remains hidden during the whole study procedure and data analysis. As such, the patients, the study team, the treating physician, the operation team (i.e., surgeon/anesthesiologist), and the outcome assessors will be blinded. The unblinding will be performed after completion and data analysis. Via a separate login in Castor EDC, the pharmacy can view the result of the randomization and prepare the study medication. The study medication is a 100-ml clear NaCl 0.9% solution with no visual difference between the placebo of the tranexamic acid group. As such, the blinding remains intact for the team.

### Procedure for unblinding if needed {17b}

Emergency unblinding will only be performed in case of any adverse or serious adverse event which is unexpected and out of proportion with the standard of care. Unblinding will be performed by a member of the primary research team. All involved research member can reach the member of the primary research team 24/7.

## Data collection and management

### Plans for assessment and collection of outcomes {18a}

By standardizing the study procedure using a Standard Operation Procedure (SOP) the data collection, measurement and timing of blood samples will be equal in all study sites. The study team will be trained to perform and guide the perioperative study procedure. The measurement of blood loss is standardized and twofold to create higher accuracy. All data will be collected digitally.

### Plans to promote participant retention and complete follow-up {18b}

This is not applicable. The whole study period will be performed while the participants are in the hospital, and participants can therefore be directly monitored.

### Data management {19}

All data will be entered and stored digitally in the Castor EDC environment. Castor EDC provides account/password-protected access to the database. The study team and principal investigator can assign different rights to each individual, for example to read and write. When creating a new record, Castor EDC will automatically create an ID for the patient based on inclusion site, number of inclusions of that specific site, and treatment arm. This ID will be used for all future reference with data and blood samples regarding this patient. The handling of personal data will comply with the Dutch Personal Data Protection Act and Data will be stored for 15 years.

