### Participant timeline {13}

When a potential participant is scheduled for burn excisional surgery, the patient is informed about the study and informed consent is taken. See Fig. 1 for the complete timeline for the participant. Informed consent is usually taken in the 2-3 days before surgery. After consent, the patients are randomized. A blood sample is taken before surgery to establish a baseline. During surgery, two more blood sample will be taken, and one blood sample will be taken 6–12 h after surgery. Hereafter, the study procedure is finished for the patient. After 3 months, the patient will be contacted to inform whether cardiopulmonary of neurologic complications have occurred.

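### The patient ID is described as built partly from the treatment arm, which contradicts the plan's own statements on blinding and concealment

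*Protocol article*

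**What the plan says.** All references are to the protocol article.

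- **Data management {19}** describes how the identifier is made: "When creating a new record, Castor EDC will automatically create an ID", and the ID is based on three elements, the third being the arm: "an ID for the patient based on inclusion site, number of inclusions of that specific site, and treatment arm". Its use is general: "This ID will be used for all future reference with data and blood samples regarding this patient".
- **Who will be blinded {17a}** states: "The randomization result will be held in the Castor EDC program which remains hidden during the whole study procedure and data analysis". It lists those covered: "the patients, the study team, the treating physician, the operation team (i.e., surgeon/anesthesiologist), and the outcome assessors will be blinded". The pharmacy alone sees the result, through its own login.
- **Sequence generation {16a}** says the study team is kept unaware of the sequence and of current and earlier allocations. Allocation is 1:1, stratified by site, in variable blocks: "The block size will be set to 2, 4, and 6".
- **Concealment mechanism {16b}** says the study team cannot see the randomization process.
- **Trial design {8}** extends blinding to the statistical procedure.
- **Confidentiality {27}** calls the identifier a coded number and limits database access to the research team.
- **Participant timeline {13}** gives the order: "After consent, the patients are randomized".

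No section says that the arm element is masked, encrypted or left out of the ID that staff see.

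**The concern.** An identifier that contains the arm is in front of everyone who opens a record or handles a labelled tube. A neutral code such as A or B does not name the drug, but it still divides the patients correctly into their two groups. Once one patient is unblinded in an emergency, the meaning of the code is known for all of them.

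The ID also contains the site and the inclusion number at that site. Put in order, the IDs would show each site's allocation history, which {16a} says is concealed. In small site-stratified blocks, a visible history makes the next allocation partly predictable. Eligibility depends partly on the surgeon's estimate of expected blood loss (Eligibility criteria {10}), so predictability could in principle affect who is enrolled.

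The staff most plausibly exposed are the study team, who have database access. The dedicated person described in Intervention description {11a} registers blood loss and measures the excision, which together give the primary outcome in ml per % BSA excised. The planned analysis is also supposed to be blind.

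**Working it through.** **1. The statements side by side**

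| Question | Data management {19} | Sections {16a}, {17a} |
|---|---|---|
| Does anything used by the study team depend on the arm? | Yes, the ID | No, the result is hidden |
| Where does it appear? | All data and blood samples | Pharmacy login only |
| Are earlier allocations at a site visible? | Yes, if the arm can be read from the ID | No |

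The general assurance in {17a} does not resolve the specific sentence in {19}; it is the statement that {19} contradicts.

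**2. How predictable the next allocation would be**

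The plan gives no figure on this point, so there is none to reproduce. Inputs from {16a}: 1:1 allocation, stratification by site, block sizes 2, 4 and 6. Assumptions: past arms (or arm codes) at the site can be read, and the three block sizes are equally likely. The article gives the sizes but not their mix.

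The strategy is to guess the arm that is behind so far at the site, and to toss a coin when the arms are level. It needs only the running imbalance, not the block size. For a block of 2b patients, the expected number of correct guesses is

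b + (4^b / C(2b, b) − 1) / 2

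- Block of 2 (b = 1): 1 + (4/2 − 1)/2 = 1.5, so 1.5/2 = 75%.
- Block of 4 (b = 2): 2 + (16/6 − 1)/2 = 2.83, so 2.83/4 = 71%.
- Block of 6 (b = 3): 3 + (64/20 − 1)/2 = 4.1, so 4.1/6 = 68%.
- Equal mix: (1.5 + 2.83 + 4.1)/(2 + 4 + 6) = 8.43/12 = 70%.

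Under concealment the rate is 50%.

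**3. Cross-check by simulation**

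One site's sequence was simulated with past arms known and block sizes hidden, 3,000 runs for each site size. The share of correct guesses was 0.695 for 16 patients, 0.699 for 32 and 0.699 for 63. For 16 patients, the minimum per centre mentioned in {16a}, this is 0.695 × 16 = 11.1 correct guesses against 8 by chance.

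**4. How often the next allocation would be certain**

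With block sizes hidden, about 4% of allocations are certain. If the current block size were also known, the shares would be 50%, 33% and 25% for blocks of 2, 4 and 6. Predictable here therefore means better than chance, not known.

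**5. After the change**

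With the arm out of the ID and past arms hidden, the rate returns to 50%. The sample size is not affected.

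**The case against.** The strongest reply is that the article shows a contradictory sentence, not a working leak. The ID format is not given, {19} says only that the ID is based on the arm, and {27} calls it a coded number. The order of events also makes the literal reading doubtful. The ID is created with the record, while randomization follows consent and the allocation is generated on demand (Implementation {16c}). If the record is opened before randomization, its ID cannot yet contain the arm. The text does not fix that order, so a drafting slip is possible but not shown. This objection stands as a limit on what can be concluded; it does not remove the contradiction.

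Three stronger readings are tempting, and the document does not support them.

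- *The blind is broken and the outcome data are biased.* Nothing shows that an arm element appears on any issued ID. Blood loss is largely measured, by canister volume, weighed materials and a hematocrit-based calculation ({11a}). The surgeon and anesthesiologist decide on hemostatic measures and transfusion ({11d}), but they are not shown to see the ID. Labels might be visible in theatre; the article does not say.
- *Staff could steer patients to tranexamic acid with 70% success.* That requires readable past arms and someone tracking the sequence at the site. With a neutral code, the 70% is the chance of guessing the code. It becomes the chance of guessing the drug only once the code is known.
- *The emergency procedure in {17b} is also wrong, because "Unblinding will be performed by a member of the primary research team".* An exceptional code-break by a designated, always reachable person does not contradict {17a}, and nothing says that this person has standing access to allocations. A preference for another route corrects no error in the document.

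**Conclusion.** The contradiction is real and needs correcting: {19} puts the treatment arm into an identifier used on all data and samples, while {16a} and {17a} say that allocations are hidden from the people who use it. Followed as written, {19} would compromise both the blinding and the concealment of later allocations.

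The size of the consequence is conditional. If the arm or an arm code can be read from the ID, the two groups are separated for anyone who sees it, one emergency unblinding identifies both, and the next arm or code is guessed correctly about 70% of the time instead of 50%. The range is 68% to 75% across single block sizes, and the 70% rests on an equal mix. If the sentence is a slip and the ID carries no arm element, only the wording is at fault. The article does not allow a choice between these cases; the sponsor can settle it by looking at the issued IDs.

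**What to change.** 1. Reword Data management {19} so that the ID is built from inclusion site and sequential inclusion number only, and state that the arm is held solely in the pharmacy view. This brings the section into line with {16a} and {17a}.
2. Check whether any ID or sample label already issued carries an arm element, coded or not, and record the answer.
3. Only if one does: re-key the records and stored samples, and document who could have seen the arm element and from when, so that possible unblinding can be reported with the results.

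Steps 1 and 2 cost a sentence, at most a database setting, and a short check. Step 3 is a one-off re-keying. Trial status gives December 2025 as the expected end of inclusion, and samples are stored for later analysis, so the change would protect patients still to be enrolled and later laboratory readings. Sample size and analysis are unchanged.

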### Confidentiality {27}

The Castor EDC will be used to collect and store all data. Castor EDC is compliant with the ICH E6 GCP, GDPR, and HIPAA and is ISO 270001 and ISO 9001 certified. The participants will be identified by a coded ID number to maintain participant confidentiality. The identification fill will be stored separately in a password-protected folder in the hospital’s network. Only members of the research team can access the Castor EDC and the identification file.

### Plans for collection, laboratory evaluation, and storage of biological specimens for genetic or molecular analysis in this trial/future use {33}

Blood samples will be primarily collected via the intravenous line which is already in place (due to surgery). However, when not possible, the samples will be collected via venipuncture. In every patient, several blood samples will be taken. One part of the samples will be directly analyzed by the lab (e.g., ROTEM, coagulation etc.); the other part of the sample will be processed (by the standard operation procedure of the clinical chemistry lab) and stored in − 80 freezers for a more detailed analysis of the coagulation (e.g., global fibrinolysis) and for future analysis and projects. The samples will be kept for a maximal of 5 years after the completion of the study, after which the samples will be destroyed. The other data will be kept for a total of 15 years. All patients give specific written informed consent for the storage of the biological specimens.

## Statistical methods

### Statistical methods for primary and secondary outcomes {20a}

Blood loss will be tested for normal distribution; if normally distributed, the mean with standard deviation will be reported, and differences between the two groups will be tested using Student’s *T*-test. Otherwise, a median with a 25–75% confidence interval will be reported and differences will be tested using a Mann-Whitney *U* test. For secondary outcome parameters, continuous variables (i.e., volume of blood loss, extent of hyperfibrinolysis) will be tested for normal distribution. If they are normally distributed, the mean with standard deviation will be reported and differences will be tested using Student’s *T*-test. Otherwise, a median with a 25–75% confidence interval will be reported, and differences will be tested using a Mann-Whitney *U* test. Binomial data will be reported using percentages, and differences will be tested using chi-squared tests.

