### Eligibility criteria {10}

#### Inclusion criteria

Patients scheduled for burn excisional surgeryAn expected blood loss of ≥ 250 ml based on the estimation by the performing surgeon based on:◦ ≥ 2% body surface area excision planned (100–200 cc/%BSA excised, based on retrospective data from Burn Centre Rotterdam)◦ Operation technique used (some techniques show more blood loss than others)◦ Time after burn trauma (i.e., expected healing and subsequently the extent of bleeding)  ≥ 18 years oldInformed consent of patient or legal representativePatients or legal representative should have enough knowledge of Dutch to provide informed consent

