### Sample size {14}

In a small retrospective group of 109 patients (unpublished) with ≥ 250 ml blood loss from Burn Centre Rotterdam, we found a mean blood loss of 1.01 ± 0.56 ml/cm^2^ or 194 ± 81 ml/% BSA excised. In a small blinded RCT study, Jennes et al. found a reduction of 36% in blood loss in 27 tangential burn wound excisions when administering tranexamic acid [12]. A small RCT with 50 patients performed in India showed a reduction of 41% blood loss in burn patients when using tranexamic acid [13]. Orthopedic literature shows a somewhat more limited blood loss reduction of approximately 25% with the use of 1–2 g of tranexamic acid during surgery [20, 22, 23]. Therefore, based on a mean blood loss of 194 ml/% BSA excised with an SD of 81 ml, demonstrating a 25% reduction in blood loss with type I and type II error rate of 5% and 20% respectively, we require 45 patients per arm, for a total of 90 patients. Taking a dropout rate of 5% into account, we aim to include 95 patients in our study.

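### The primary analysis lets a normality test choose the test, leaves out the centre strata used in randomisation, and gives no confidence interval for the 25% reduction

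*Protocol article*

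**What the plan says.** Under Statistical methods for primary and secondary outcomes {20a}, the primary test follows from a look at the outcome data: "Blood loss will be tested for normal distribution; if normally distributed, the mean with standard deviation will be reported", and Student's t-test compares the arms. If not, "a median with a 25–75% confidence interval will be reported" and a Mann-Whitney U test is used. Neither branch has a term for centre or any other baseline variable. Neither mentions a between-arm difference or ratio, or an interval for one.

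Sequence generation {16a} states: "Variable block randomization will be used, stratified by study site". Trial design {8} says the same.

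The sample size {14} is built on a relative effect: "demonstrating a 25% reduction in blood loss with type I and type II error rate of 5% and 20% respectively". It is "based on a mean blood loss of 194 ml/% BSA excised with an SD of 81 ml", and it concludes that "we require 45 patients per arm, for a total of 90 patients".

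The inclusion criteria name influences on bleeding that the surgeon should weigh when predicting blood loss, among them operation technique and "Time after burn trauma (i.e., expected healing and subsequently the extent of bleeding". The primary outcome {12} is blood loss per % BSA excised, so excised area already enters through the denominator.

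**The concern.** Three features of the stated analysis do not fit the design.

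1. **The estimand depends on the data.** A t-test addresses a difference in means. A Mann-Whitney test addresses a shift in ranks. Which of them the trial reports is decided by a preliminary test on the outcome.
2. **The analysis does not follow the randomisation.** Stratifying by centre balances the arms within centres. The true variance of the treatment difference then excludes between-centre variation, but an unadjusted test still counts that variation in its standard error. If centres differ, the test is conservative and some precision is lost.
3. **The effect the trial is powered on gets no interval.** A reader will want the percent reduction and its uncertainty. The stated output is a summary per arm and a p-value. The range labelled a confidence interval describes the spread of patients. It does not describe uncertainty about a median or about the treatment effect.

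With about 90 evaluable patients, what is at stake is interpretability and a small amount of precision that costs nothing to recover.

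**Working it through.** **Inputs from the protocol.** Control mean 194 and SD 81 ml per % BSA; 25% reduction; type I error 5%, type II error 20%; 45 per arm; three centres as randomisation strata. Sidedness is not stated. Two-sided is assumed, because it reproduces the plan's figure while a one-sided calculation gives 35 per arm.

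**Inputs that are assumptions.** The share of outcome variance due to centre (5, 10, 20%), the variance explained by other baseline covariates (10, 20, 30%), and the shape of the distribution (normal or lognormal). The protocol gives none of these.

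**Step 1: the plan's own figure.** Difference = 0.25 × 194 = 48.5. Standardised effect = 48.5 / 81 = 0.599. The exact two-sample t-test needs 44.77, so 45 per arm, and its power at 45 is 80.2%. Then 90 / 0.95 = 94.7, so 95. The stated sample size reproduces.

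**Step 2: does the pre-test cost power or size?** Simulation of 10,000 trials per setting, 45 per arm, Shapiro-Wilk on the pooled data (the protocol does not name the normality test):

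| Data | Type I error, two-step rule | Power: two-step | t-test | Mann-Whitney | t-test on logs |
|---|---|---|---|---|---|
| Normal | 4.7% | 80.1% | 80.2% | 78.0% | not relevant |
| Lognormal, same mean and SD, 25% proportional reduction | 4.8% | 90.6% | 89.5% | 90.6% | 91.7% |

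The two-step rule is about as good as either test alone. What it changes is the branch taken. With Shapiro-Wilk applied to each arm, both arms pass in about 7% of trials with lognormal data, 25% with gamma data and 90% with normal data, all at the plan's coefficient of variation of 81/194 = 0.42. So the reported quantity turns on a shape that is not yet known.

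**Step 3: size of the test when centre is ignored.** With arms balanced within centres and a share ρ of variance between centres, the unadjusted t statistic is too small by a factor of about √(1 − ρ). The actual two-sided error is then about P(|t₈₈| > 1.987 / √(1 − ρ)):

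- ρ = 0.05: threshold 2.039, error 4.4%
- ρ = 0.10: threshold 2.095, error 3.9%
- ρ = 0.20: threshold 2.222, error 2.9%

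Simulation with three equal centres on the log scale gives 4.4, 3.8 and 3.0%. With unequal centres (assumed 50/24/16) on the normal scale it gives 4.3, 4.2 and 3.3%. The test is conservative in every case.

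**Step 4: power gained by adjusting for centre.**

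| Centre share | Lognormal, CV 0.42: unadjusted → adjusted | Normal, standardised effect 0.60: unadjusted → adjusted |
|---|---|---|
| 5% | 92.5 → 93.2 (+0.7) | 80.6 → 82.2 (+1.6) |
| 10% | 92.8 → 94.4 (+1.6) | 81.9 → 84.6 (+2.7) |
| 20% | 94.5 → 96.8 (+2.3) | 82.5 → 88.2 (+5.7) |

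**Step 5: power from a further baseline covariate.** The residual SD is 81 × √(1 − R²). At 45 per arm, an assumed R² of 10, 20 or 30% gives 84.2, 88.1 or 91.9% power.

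**Step 6: what the missing interval would show.** On the planning values, the 95% half-width for the difference is 1.987 × 81 × √(2/45) = 33.9 ml per % BSA, and 33.9 / 194 = 17.5 percentage points. Treating the control mean as known, an observed 25% reduction would carry an interval of about 7.5% to 42.5%. A p-value and two medians do not convey that width.

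**The case against.** The strongest reply is that nothing here is invalid. An unadjusted test after stratified randomisation does not inflate type I error, the planned power is met, and the pre-test does almost no measurable harm. All of that stands. A reader might infer from the choice of method that the trial is underpowered or that the pre-test loses power. Steps 1 and 2 support neither.

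A reader might also infer that the protocol ignores every driver of bleeding that it names. It does not: excised area is in the outcome's denominator. Technique and time since burn are listed only as inputs to the surgeon's eligibility estimate, and the article does not say that either is recorded as an analysable baseline variable. Leaving them out is a lost opportunity, not an error.

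Larger gains from centre adjustment, of roughly 4 to 6 points, can be obtained with lognormal data at a coefficient of variation of about 0.55. That matches the ml/cm² figures (0.56 / 1.01), which the sample size does not use. On the scale the plan does use, the lognormal gain is 1 to 2 points.

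It can also be said that a crude percent reduction can be read from the two arm summaries, and that effect measures and intervals are often left to an analysis plan. The first is true, so it would be wrong to say that no estimate is possible. The second has less force, because the article does not leave the primary method open. It states a complete procedure: the tests, the rule for choosing between them and the summaries to report. The mislabelled interquartile range is a wording error whatever another document says.

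**Conclusion.** The point holds in a limited form. The choice of test, and with it the quantity compared, depends on the outcome data. Centre is a randomisation stratum but not part of the analysis. The planned output has no confidence interval for the reduction on which the trial is powered, and an interquartile range is called a confidence interval.

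The consequence is mainly one of interpretation. In operating characteristics it is a conservative test, at about 4.4, 3.8 or 3.0% for centre shares of 5, 10 or 20%. The forgone power is about 1 to 2 points under lognormal data at the plan's coefficient of variation, and about 2 to 6 points under normal data at its standardised effect. Every one of these sizes rests on an assumed variance share. If centres do not differ, nothing is lost in size or power. The change is worth making because it is nearly free, not because the present test is invalid or the trial too small.

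**What to change.** Drop the normality pre-test and prespecify, before unblinding, one primary model: linear regression of log(ml per % BSA excised) on treatment and centre. Time since burn may be added as a single prespecified baseline covariate, provided it is recorded for all patients. Back-transform the treatment coefficient and report it as a percent reduction with a 95% CI. Keep a centre-stratified rank test (van Elteren) as a sensitivity analysis. Rename the 25–75% range an interquartile range in both places where {20a} uses the phrase.

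The cost is a change of wording and a few degrees of freedom: two for centre, and one more if time since burn enters linearly. The effect also becomes a ratio of geometric means instead of a difference in arithmetic means. That matches a target expressed as a percent reduction, but the report should say so. The protocol expects inclusion to run to December 2025 and places unblinding after data analysis {17a}, so its own timetable leaves room to fix the model before allocation is known.
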